### Outcome Measures

The primary outcome of the study is the change in the DAS-28 score (with ESR) [18] and it is assessed at baseline and the end of the treatment (84th day). Secondary outcomes include the change in disease-specific biochemical and inflammatory markers (RA factor, C-reactive protein, and ESR) and serum immunoglobulin levels (Immunoglobulin G and Immunoglobulin M), participants’ assessment of Pain, Global assessment of disease activity, change in Disability Index score and frequency of use of conventional analgesic/NSAIDs medicines and occurrence of adverse events if any. The change in disease-specific biochemical and inflammatory markers and serum immunoglobulin levels are assessed at baseline and on the 84th day. The participants’ assessments for pain and global assessment of disease activity are assessed using the visual analog scale [19] ranging from 0 mm (no pain) to 100 mm (worst possible pain) at baseline, 28th day, 56th day, and 84th day. The change in Disability Index score is assessed using the Indian Health Assessment Questionnaire [20] at baseline, 28th day, 56th day, and 84th day. The frequency of use of conventional analgesic/NSAIDs medicines and occurrence of adverse events are also assessed in a time frame of baseline, 28th day, 56th day, and 84th day (Figure 1).

### Sample Size

Due to the low prevalence of RA (around 0.7% to 1%) [21], it is not feasible to recruit the participants based on the scientific line of sample size theory. Therefore, based on feasibility and the availability of resources, a total of 240 participants have been recruited from 6 institutes (40 participants at each center), within the given time frame.

### Recruitment

The eligible participants have been screened for inclusion and exclusion criteria from the outreach out-patient departments/ camps/door-to-door visits conducted in the identified area/ village under the selected study sites. The participants have been informed about the study in detail (in their regional language) through banners and IEC materials.

### Allocation

Since the study is conducted in a black box study design and the intervention is classified based on major disease patterns, allocation does not apply to this study.

### Data Collection Methods

Demographic data, clinical history, details of concomitant medications, the score of 2010 American College of Rheumatology and the European League Against Rheumatism criteria, DAS-28, and other assessment parameters of the participants have been recorded in the CRF. The participants were followed up on the 28th day, the 56th day, and the 84th day**.** During follow-ups, the occurrence of any symptom and the need for any rescue medication have been recorded. The contact number of the investigator along with the address of the CCRAS institute have been provided to the participants at the time of enrollment**.** Participants have been instructed to inform about any adverse event that happens during the study period**.**

Besides a hard copy of CRF, the data have been recorded in e-CRF also. All source documentation supporting entries into the CRFs are maintained and will be kept readily available. To ensure the quality, the data are checked for consistency, omissions, and any apparent discrepancies. The reason for withdrawal or dropping out of participation is recorded in the CRF.

### Data Monitoring

A Data Safety Monitoring Board has been constituted to monitor the clinical study and to ensure the safety of the participants. The inspection of various records of the clinical study (CRFs and other pertinent data) will be done by the CCRAS representatives and regulatory authority to ensure strict adherence to the study protocol and correct documentation of the data. Any problems faced by the research staff at the participating site have been addressed timely. The Clinical Monitoring Committee is responsible for verifying the CRFs at regular intervals throughout the study to verify adherence to the protocol; completeness, accuracy, and consistency of the data; and adherence to local regulations on the conduct of clinical research.

### Deviation From the Protocol

Any deviation from the study protocol is implemented in the study only after approval from the IEC.

### Ethical Considerations

The study is conducted according to the national ethical guidelines for biomedical and health research involving human participants (2017) by the Indian Council of Medical Research; and Good Clinical Practice guidelines for clinical trials in Ayurveda, Siddha, and Unani Medicine, 2013. Approval from the IEC of all the concerned institutes has been obtained, and the study has been registered with the Clinical Trial Registry-India (CTRI/2023/06/054203 dated June 20, 2023). The participants have been educated by the investigator verbally and using a written patient information sheet in their regional language and have been asked to provide consent in writing regarding their participation in the study. The participants have been made aware that they are free to leave the study if they wish to discontinue without giving a reason, and without my medical care or legal rights being affected. All the information and records of the study participants including their names and identities are kept confidential in password-protected Microsoft Excel sheets. All the study participants are covered by a clinical trial insurance policy which included coverage for any adverse events occurring during the study.

### Statistical Analysis

After data collection, verification of its accuracy and limits will be done. The filtered data will be used for additional analysis and interpretation. The Categorical variables will be reported in number (percentage) and analysis of pre-post-trial outcomes will be done by the Mc-Nemar chi-square test. The continuous variables (like scores and lab parameters) will be analyzed by paired *t* test/Wilcoxon test as per the distribution of data in the pre-post trial situation. The assessment parameters assigned in more than 2 follow-ups will be analyzed using the r-ANOVA/Friedman test/ Cochran Q test. The continuous data having normal distribution will be represented as mean (SD) and the data not having normal distribution as median (IQR). The 5% level of significance will be used throughout the analysis. The SPSS (version 26.0; IBM Corp) software will be used to conduct the analysis.

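### The tests named for the four-visit secondary outcomes use complete cases only and do not estimate the day-84 change; a repeated-measures model with a named contrast would be better

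*Protocol article*

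**What the plan says.** The Outcome Measures section schedules four secondary outcomes at baseline and days 28, 56 and 84: pain and global assessment on a 100 mm visual analogue scale, disability, and use of conventional analgesics or NSAIDs. Disability is defined as a change: "change in Disability Index score is assessed using the Indian Health Assessment Questionnaire". The primary outcome, DAS-28 with ESR, is taken only at baseline and day 84.

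The Statistical Analysis section gives one rule for outcomes with several follow-ups: "The assessment parameters assigned in more than 2 follow-ups will be analyzed using the r-ANOVA/Friedman test/ Cochran Q test". Continuous variables with one before and one after value "will be analyzed by paired *t* test/Wilcoxon test as per the distribution of data in the pre-post trial situation". On error rate it says: "The 5% level of significance will be used throughout the analysis". Summaries are mean (SD) or median (IQR); no confidence intervals are mentioned.

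The Sample Size section states that "a total of 240 participants have been recruited from 6 institutes (40 participants at each center". The Results section reports that 222 of 240 (92.5%) completed. The Withdrawal Criteria section lists unwillingness to continue, worsening RA symptoms, development of an excluded illness, and adverse events as grounds for withdrawal.

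**The concern.** Repeated-measures ANOVA in its usual form, the Friedman test and Cochran's Q all work on a complete participant-by-visit table. Someone who attended baseline, day 28 and day 56 and then left contributes nothing, although three of four values were recorded.

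Two consequences follow. First, if people leave because they are doing badly, those who remain look better than the enrolled group. A single-arm before-after study has no control arm in which a similar selection could offset this. Second, all three are omnibus tests. A small p-value says that the visits are not all alike. It does not give the size of the change at the end of treatment, which is what the outcome definitions ask for.

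A lesser question is centre. Participants come in blocks of 40 from six institutes, and none of the named tests uses centre. If the change itself differs from centre to centre, and the result is meant to apply beyond these six, the planned p-values can be too small.

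**Working it through.** **Inputs from the protocol article.** Enrolled: 240 in six centres of 40 (Sample Size). Completed: 222 (Results). Time points: four for the secondary outcomes above, two for DAS-28 (Outcome Measures). Level: 5%, taken as two-sided because the side is not stated.

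**Inputs assumed.** Proportion of completers missing each interim visit: 0 to 10%. Intraclass correlation (ICC) of the change score within centre: 0 to 0.05. Completers spread evenly over centres: 222/6 = 37. The article gives none of these.

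**The article's own figures.** 6 × 40 = 240 and 222/240 = 0.925. Both reproduce. There is no power calculation to check.

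**Step 1: participants dropped from the four-visit tests.** Non-completers: 240 − 222 = 18, and 18/240 = 7.5%. This is the minimum without imputation. If a proportion q of completers misses each of days 28 and 56 independently, the complete-case n is 222 × (1 − q)²:

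| q (assumed) | complete-case n | dropped from 240 |
|---|---|---|
| 0 | 222 | 7.5% |
| 2% | 213 | 11% |
| 5% | 200 | 16.5% |
| 10% | 180 | 25% |

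**Step 2: precision.** The standard error with 222 rather than 240 is larger by √(240/222) = 1.04. This is the most that could be regained from the 18, since partial records carry less than full ones. Precision is therefore not the main issue.

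**Step 3: possible bias.** Let δ be the amount by which the mean day-84 change of the 18 would have been worse than that of the 222. The completers' mean overstates the benefit in all 240 by (18/240) × δ = 0.075 δ. On the 100 mm scale, each 10 mm of δ moves the mean by 0.75 mm. Neither δ nor the reasons for leaving are reported.

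**Step 4: centre.** A centre difference in level cancels in a within-person change; only variation between centres in the change matters. The design effect is 1 + (37 − 1) × ICC, and the standard error is understated by its square root:

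| ICC of change (assumed) | design effect | SE ratio | coverage of a nominal 95% paired-t interval, centres in general | same, these six centres only |
|---|---|---|---|---|
| 0 | 1.00 | 1.00 | 95% | 95% |
| 0.01 | 1.36 | 1.17 | 91% | 95% |
| 0.05 | 2.80 | 1.67 | 76% | 96% |

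Coverage is from 20,000 simulated trials per row with 6 × 37 completers. A t interval on the six centre means (5 df, critical value 2.571) covered 95% in every row.

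**The case against.** The article condenses a fuller protocol, and imputation or a centre analysis may be set out in a document not shown. That stands: the absence of a missing-data method or a centre term is not a fault here. The point rests on the tests that the article does name, which need complete rows unless something is imputed.

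The paired t or Wilcoxon rule for continuous scores could also supply a day-84 change. This stands in part, but the article sends outcomes with several follow-ups to the omnibus tests and names no contrast for them.

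Friedman's test makes no normality assumption, and pain and disability scores may be skewed. This also stands as a cost of the replacement.

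Four stronger readings are tempting and are not supported:

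- *The planned intervals are too narrow.* No intervals are planned. No ICC is given, and the effect is nil at an ICC of 0 or if inference stops at these six centres.
- *A mixed model cures both problems.* A random centre intercept cancels in the change and leaves its standard error as it was; an effect of centre on the change would be needed. With six centres, that approach with normal-theory (Wald) limits covered only about 90% at an ICC of 0.05. For missing data, the model is valid only under missing at random, which withdrawal for worsening may breach.
- *Participants left because they worsened.* Worsening is a permitted ground, but the reasons for the 18 are not reported.
- *The primary result loses recoverable data.* DAS-28 has no interim values to recover.

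**Conclusion.** The point holds for the four-visit secondary outcomes. As named, the tests discard at least 7.5% of those enrolled unless values are imputed. The loss would be 11% to 25% if 2% to 10% of completers missed each interim visit. The tests also do not estimate the change of interest. The direction of any bias is plausibly towards benefit, given the grounds for withdrawal, but its size cannot be stated; it is 0.075 times an unknown difference, before intermittent misses. The cost in precision from the 18 is small, at most a factor of 1.04.

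The centre point is conditional and secondary. For an assumed ICC of change of 0.01 to 0.05 and inference beyond these six institutes, standard errors are understated by a factor of 1.17 to 1.67. At an ICC of 0 they are not understated at all. It justifies a check, not a claim that the planned p-values are wrong.

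**What to change.** In the Statistical Analysis section, replace repeated-measures ANOVA and Friedman with one linear mixed model per continuous four-visit outcome. Use baseline and the three follow-ups as responses, visit as a category, an unstructured within-person covariance and all 240 enrolled. Name day 84 minus baseline as the contrast and report it with a 95% interval. For NSAID use recorded as yes or no, replace Cochran's Q with a logistic mixed model or GEE. Note that ordinary GEE needs a stricter missing-data assumption than the mixed model.

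State that the mixed models assume missing at random. Add a sensitivity analysis in which those withdrawn for worsening or adverse events are given day-84 values less favourable than the model predicts, over a stated range. If scores are clearly skewed, keep the Friedman or Wilcoxon result as a supporting analysis.

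For DAS-28 and the repeated outcomes, list the six centre mean changes and their 5-df t interval as a secondary check.

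The cost is programming, a missing-at-random assumption that must be defended, and a wider interval in the centre check if centres differ. No new data are needed. Follow-up is complete and analysis is under way, so the change needs a dated amendment before results are seen. The article's section on deviations also calls for ethics committee approval. If results have already been seen, the new analyses should be labelled as chosen afterwards.

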## Results

The enrolment of the participants in the study was initiated in December 2023 and the final follow-up was completed in March 2024. Out of 240 participants enrolled, 222 (92.5%) participants have completed the study. Data verification, compilation, and analysis are under process. The findings from the study will be published in peer-reviewed journals after the completion of data analysis.

## Discussion

### Expected Findings

The selected composite Ayurvedic regimen is anticipated to reduce DASs in study participants with RA. This study was designed using a black box approach, which allows for the selection of medicine according to the pattern of disease presentation and associated symptoms instead of evaluating a specific medicine for a particular diagnosis [10].

Ayurvedic approach to treating a disease depends on the breaking of pathogenesis and alleviation of symptoms. The selection of medicines depends on different stages of pathogenesis that are usually assessed by the presentation of the disease. The available studies for the evaluation of Ayurvedic interventions in rheumatoid mostly used study designs such as single-arm studies, non-RCTs, and RCTs using controls from either Ayurveda or modern conventional drugs [22-25]. In these studies, the intervention was the same for all participants diagnosed with RA and did not consider differences in clinical conditions or the relationships with *Dosha* or *Ama*. Furst et al [26] have used modified RCT as a double-blind, randomized, double-dummy design to evaluate the efficacy of Ayurvedic medicines, both alone and in combination with the standard drug, methotrexate. In this study, 148 distinct Ayurvedic formulations with various dosage forms were used, allowing physicians to prescribe the appropriate combination of drugs based on the specific needs of the patient [26]. In our study, we have designed a single-arm black box design that allows the management of RA in different clinical manifestations on the basis of pathogenesis in terms of the association of *Ama* and *Dosha* along with the chronicity of the disease. For this, a predefined composite Ayurvedic regimen was used that is anticipated to reduce DASs in study participants with RA along with a change in disease-specific biochemical markers. Ayush-SG and *Rasnasaptak Kashaya* were given to all participants, while other medications were customized as per the form of disease presentation.

Ayush-SG contains 3 main ingredients as follows: *Shunthi* (*Zingiber officinale* Roscoe), *Guggulu* (*Commiphora wightii* Bhan), and *Godanti Bhasma* (Incinerated calcium sulfate/ gypsum) [12]. *Shunthi* is known to have anti-inflammatory, analgesic, immunomodulatory, and antioxidant activities [27]. Studies show that guggulipid, the oleo-gum resin of the plant *Commiphora wightii*, demonstrates significant antiarthritic and anti-inflammatory effects by targeting key molecular pathways involved in inflammatory responses [28,29]. *Rasnasaptak Kashaya* contains *Shunthi* along with other herbal ingredients such as *Rasna* (*Pluchea lanceolata* Oliver and Hiem), *Gokshura* (*Tribulus terrestris* L), *Guduci* (*Tinospora cordifolia* [Willd] Miers), *Punarnava* (*Boerhaavia diffusa* Linn), *Eranda* (*Ricinus communis* Linn), *Devadaru* (*Cedrus deodara* [Roxb] Loud), and *Aragvadha* (*Cassia fistula* Linn). All these drugs possess anti-inflammatory activities and *Gokshura*, *Eranda*, and *Devadaru* have analgesic properties also. *Rasna* and *Guduci* have antiarthritic and *Aragvadha* has antirheumatic properties additionally [30-36]. A previous study on *Vatari Guggulu*, *Rasnasaptak Kashaya*, and *Brihat Saindhavadi Taila* has shown a significant change in DAS-28, disability index (Indian Health Assessment Questionnaire), and quality of life assessment (SF-36) scores when administered for 12 weeks [37].

*Guduci Ghanavati* contains an aqueous extract of *Tinospora cordifolia,* which possesses antiarthritic, anti-inflammatory, immunomodulatory, and antipyretic properties*.* The in vivo studies on aqueous extract of *T cordifolia* showed significant anti-inflammatory effects comparable with indomethacin and the mode of action is opined to be similar to that of a nonsteroidal anti-inflammatory agent [36].

*Brihat Saindhavadi Taila* is described as effective in pacifying pain in Amavata [37]. It is found effective in alleviating pain, swelling, and tenderness when administered locally in combination with other internal medications [14,38]. Most of the ingredients in this formulation possess anti-inflammatory properties [39-44]. *Eranda,* the base oil in the formulation, contains ricinoleic acid that has shown anti-inflammatory properties on peripheral application in an in vivo study in guinea pigs [45].

*Dashanga lepa* consists of 10 ingredients as follows: *Sirisha* (*Albizzia lebbeck* Benth), *Madhuyashti* (*Glycyrrhiza glabra* Linn), *Tagara* (*Valeriana wallichii* DC), *Raktachandanam* (*Pterocarpus santalinus* Linn), *Ela* (*Elettaria cardamomum* [Linn] Maton), *Jatamansi* (*Nardostachys jatamansi* DC), *Haridra* (*Curcuma longa* Linn), *Daruharidra* (*Berberis aristata* DC), *Kushta* (*Saussurea lappa* CB Clarke), and *Hrivera* (*Pavonia odorata* Willd). Most of the ingredients in this formulation have potent anti-inflammatory properties, and *Tagara* and *Jatamansi* have analgesic action too [46-54]. The anti-inflammatory and analgesic activities of *Dashanga Yoga/lepa* have been demonstrated in an in vivo study conducted on Wistar rats [55].

Anemia is one of the common comorbidities found in RA patients [56]. *Punarnavadi Mandura* contains ingredients such as *Amalaki* (*Phylanthus embelica* Linn), *Danti* (*Baliospermum montanum* Muell – Arg), *Pippali* (*Piper longum* Linn), *Punarnava*, *Kushtha* (*Saussurea lappa* C.B. Clarke) and *Daruharidra* (*Berberis aristata* DC) along with a mineral drug *Mandura bhasma* (incinerated iron oxide). An in vivo study conducted on *Punarnavadi Mandura* has shown significant hematinic activity against mercuric chloride-induced anemia in albino rats [57]. A previous clinical study on the drug also showed significant improvement in serum iron and serum ferritin levels with improvement in the symptoms of anemia such as fatigue, pallor, etc [58].

The pharmacological properties of the ingredients in the formulations and previous studies suggest that the selected composite Ayurveda regimen for the study will be effective in the management of RA. The findings from the study will be disseminated through reputed peer-reviewed journals after the completion of the data analysis. This research represents an initial effort using a black box design, which could lay the groundwork for customized interventions rooted in Ayurvedic concepts of pathogenesis and symptomatology.

### Strength and Limitations

This study is planned using a black box design that will help in providing evidence-based data regarding the effect of personalized medications in Ayurveda for the management of RA. However, the study protocol has some limitations also. The study protocol does not include the assessment of inflammatory markers such as anticyclic citrullinated peptide. In this study, 3 distinct categories are considered for the composite Ayurvedic regimen. Future research could be designed to address a wider variety of disease presentations.

### Future Scope

This study protocol could be extended to similar conditions that are presented with a wide range of symptoms that require a more individualized approach. Future RCTs may be planned to compare the Ayurveda treatment regimen with conventional standard treatment protocol.

### Conclusions

This interventional study that incorporates the black box approach may provide a strong framework for managing RA. This design may be a more reliable method for evaluating the effectiveness and tolerability of the composite Ayurveda regimen in RA.

## Abbreviations

CCRAS: Central Council for Research in Ayurvedic Sciences
CRF: case record form
CTRI: Clinical Trial Registry-India
DAS: disease activity score
ESR: erythrocyte sedimentation rate
HbA1c: hemoglobin A1c
IEC: Institutional Ethics Committee
NSAID: nonsteroidal anti-inflammatory drug
RA: rheumatoid arthritis
RCT: randomized controlled trial
